### Interventions

Suprasensory or subsensory RPSS was initially administered in the second experimental session (Figure 1) at HSR and at HIAE, and also in the third experimental session at HIAE. After approval of an amendment in August 2021, RPSS started to be administered in the first visit, after the assessment of the patient characteristics. This protocol corresponds to version 5 of the project and includes all the amendments approved until August 2021.

Subjects are comfortably seated during RPSS. Trains of electrical pulses (1 ms of duration for each) at a frequency of 10 Hz are delivered at 1 Hz (500 ms on and 500 ms off) to the median nerve on the wrist by one pair of surface electrodes (Kendall; cathode, proximal) connected to a customized stimulator (Alfamedic Ltda, São Paulo, Brazil; maximum output, 130 V). The median nerve is stimulated between the tendons of the flexor carpi radialis and palmaris longus with the cathode positioned 2–3 cm proximal to the wrist. Three measurements of the minimum stimulation intensity required to elicit paresthesia (sensory threshold) are performed.

For suprasensory stimulation, intensities are set at the highest intensity able to induce paresthesia without overt muscle contraction or pain and adjusted if required (21, 39, 45). In subsensory, the intensity of stimulation is below sensory threshold, not sufficient to elicit paresthesia (20).

Every 5 min, participants are asked about the sensations elicited by stimulation in order to avoid fluctuations in wakefulness and in attention to the stimulated body part (46). The intensity of stimulation is increased if paresthesia becomes weaker, and lowered if they become uncomfortable or during the 2-h period. Usually, it is necessary to adjust the intensity of stimulation due to changes in the intensity of paresthesia during the 2-h period. There may be changes in skin impedance and subjects in the RPSS group may report increase or decrease in paresthesia. The intensity of stimulation is then adjusted to elicit strong paresthesia in the absence of pain or movement. In the subsensory group, the initial intensity defined so that no sensations are elicited may lead to paresthesia during the 2-h period. When this occurs, the intensity of stimulation is lowered below the sensory threshold. During RPSS, subjects watch videos of their choice.

A single session of RPSS has been shown to improve motor performance in the absence of training (19–22, 47) and to enhance effects of training (11, 16, 18, 22). In session 3 (Figure 1), patients are initially familiarized with the JTT by performing each task once in two blocks of practice. Then, baseline assessments are performed. After suprasensory RPSS or subsensory for 2 h, the JTT scores and strength are reassessed. Then, the subjects undergo two blocks of training of tasks of the JTT under the supervision of a rehabilitation professional blinded to the type of stimulation received (22). During motor training, subjects are instructed to perform the JTT tasks that they can complete as fast as possible. Two blocks of training are administered. In each block, each task is performed once. JTT performance is reassessed after training.

Adverse events are monitored during and immediately after the stimulation. Studies included in a systematic review did not report any serious adverse events (6). Two studies described contact dermatitis on the skin under the electrode. If hyperemia is identified after stimulation, this will be reported as an adverse event. If it resolves spontaneously in 30 min, no further action is taken. If there is itching or persistent hyperemia, a topical corticoid cream may be used. In all three centers, the visits and experiments take place inside hospitals with medical resources. A specific insurance policy for clinical trials was taken for financial protection of the sponsor and researchers.

The visual analog scale (VAS) assessed before and after stimulation and after training, to grade sleepiness, fatigue, and anxiety (42).

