Likewise, the effects of RPSS on synaptic activity or concentration of neurotransmitters are unknown. γ-Aminobutyric acid in the sensorimotor cortex has been implicated in the processing of afferent input. For instance, in healthy subjects, GABA concentrations evaluated with magnetic resonance spectroscopy predict changes in perceptual outcome after afferent, tactile stimulation of fingertips (33). In rats, GABAergic inhibition modulates responsiveness to afferent stimulation of the forepaw (34). The GABA concentration or activity in M1 may influence responsiveness to RPSS. Furthermore, RPSS may also increase or decrease GABA levels in the cortex. Until now, these hypotheses have not yet been tested.

The primary goal of this study is to compare the effects of a single session of RPSS on motor performance and motor learning in subjects with stroke in the subacute (EARLYgroup) and chronic (CHRONICgroup) phases with mild upper limb motor impairments. We hypothesize that enhancement of motor performance and motor learning by RPSS will be significantly greater in subjects in the CHRONICgroup than in subjects in the EARLYgroup, when exposed to the same experimental paradigm. In addition, we compare the effects of a single session of RPSS on cerebral perfusion, changes in the BOLD effect, and on GABA levels changes in ipsilesional and contralesional M1. Our hypothesis is that changes in these outcomes will be significantly greater after RPSS in subjects in the chronic, than in the early stage.

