##### Hand Strength

Lateral pinch and grasp strength are measured with a dynamometer (Saehan grip) according to a protocol with established validity (44). In Session 3 (Figure 1), patients are initially familiarized by performing lateral pinch and grisp strength once, using the dynamometer. Then, for outcome assessments, five trials of pinch and handgrip are performed before and after stimulation (Figure 1). During each trial, the patient is instructed to perform the movement for 5 s. The average of five trials is calculated. Improvement in pinch strength after RPSS was previously described in separate studies that included patients in the subacute (8) and chronic (39) post-stroke phases (44).

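### The article contradicts itself on which session holds RPSS and the outcome tests, and pre-amendment HIAE patients may have had an outcome measured after an earlier RPSS session

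*Protocol article*

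**What the plan says.** The Introduction of the protocol article sets the exposure: "The primary goal of this study is to compare the effects of a single session of RPSS on motor performance and motor learning". The Abstract and Discussion also describe one session.

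Interventions first gives the schedule under which recruitment began: "Suprasensory or subsensory RPSS was initially administered in the second experimental session (Figure 1) at HSR and at HIAE, and also in the third" session at HIAE. It then reports the amendment of August 2021, after which "RPSS started to be administered in the first visit, after the assessment of the patient characteristics", and adds: "This protocol corresponds to version 5 of the project and includes all the amendments approved until August 2021".

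Later in the same section, in the present tense and without naming a centre, the testing sequence reads: "In session 3 (Figure 1), patients are initially familiarized with the JTT by performing each task once in two blocks of practice". Baseline follows, and then "After suprasensory RPSS or subsensory for 2 h, the JTT scores and strength are reassessed". The Hand Strength paragraph gives the same session number: "In Session 3 (Figure 1), patients are initially familiarized by performing lateral pinch and grisp strength once, using the dynamometer".

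The Primary Outcome section defines the outcome as percentage change in JTT from the pre-stimulation value. The Imaging Outcomes section says that GABA, perfusion and fMRI are measured before and after RPSS, at HIAE.

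**The concern.** Two separate matters are involved.

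First, the operative text does not agree with itself. A reader cannot tell from the prose in which session or visit the primary outcome is taken, or whether that is the same for all centres.

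Second, the original HIAE schedule contained two RPSS sessions. If an outcome was taken around the second, its pre-stimulation value was recorded after the patient had already received the allocated stimulation once. Interventions itself states that one session improves motor performance even without training, so some carry-over into a later baseline is plausible on the trial's own premises. Results from such patients would be pooled with those of patients stimulated for the first time, and all would be reported as the effect of one session.

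The primary hypothesis is that the RPSS effect is larger in chronic than in early patients. Phase is not randomized, so nothing guarantees that previously exposed patients are spread evenly over the two phases.

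**Working it through.** The point is textual, so the check sets the statements side by side.

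| Source in the protocol article | HSR | HIAE | HCFMUSP |
|---|---|---|---|
| Interventions, original schedule: RPSS in | session 2 | sessions 2 and 3 | not named |
| Interventions, since August 2021: RPSS in | first visit | first visit | first visit |
| Interventions and Hand Strength, current procedure: baseline, RPSS and retest in | session 3 | session 3 | session 3 |

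(Rows 2 and 3 make no distinction by centre.)

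**Step 1, consistency.** The change from row 1 to row 2 is amendment history and is not an error. Rows 2 and 3 both describe current procedure and do not agree. Row 3 does not fit HSR's original schedule either. The only entry of rows 1 and 2 that it fits is pre-amendment HIAE, where session 3 came after RPSS in session 2.

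**Step 2, what followed an earlier exposure at pre-amendment HIAE.** The article does not say which session held the behavioural tests and which held the MRI. The possibilities are:

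- JTT and strength in session 3, MRI in session 2: the behavioural outcomes follow an earlier RPSS.
- JTT and strength in session 2, MRI in session 3: the imaging outcomes follow an earlier RPSS.
- Both in session 3: both sets follow an earlier RPSS.
- Both in session 2: neither does. The session 3 stimulation would then have no outcome attached, and the session 3 text would be wrong for every centre.

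So unless the second stimulation served no measurement, one set of outcomes in these patients was not taken around a first exposure.

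**Step 3, how many patients.** The planned total can be reproduced: 68/0.95 = 71.6, rounded up to 72, and 48 + 24 = 72 by centre (Sample Size). The 48 pools HIAE with HCFMUSP and covers the whole recruitment period, so 48/72 = 67% is a loose ceiling and not an estimate. The affected patients are those enrolled at HIAE from December 2019 to March 2020, and from May 2021 until the August 2021 amendment took effect (Location and Setting). Their number is not printed.

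**Step 4, what an adjustment can do.** Let the arm difference be δ₀ in patients with no earlier exposure and δ₁ in patients with one, and let a share f be previously exposed, balanced between arms. A model with an arm term estimates

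(1 − f)·δ₀ + f·δ₁.

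Adding a 0/1 main effect for earlier exposure leaves this average unchanged, because the term shifts both arms equally. Recovering δ₀ needs either restriction to patients with no earlier exposure or an exposure-by-intervention term. Neither f nor δ₁ is in the article, so no numerical bias is given here.

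**The case against.** A reader might infer that HIAE patients had their primary outcome scored after a second exposure, so that one session is not what the trial analyses. The article does not support this. No sentence says which pre-amendment HIAE session held the JTT. HSR stimulated only in session 2 and imaging was done at HIAE, so session 2 may have been the behavioural session everywhere and session 3 the MRI session at HIAE. Figure 1, to which the text refers for the sessions, is not shown and may settle the order. Even in a previously exposed patient, the baseline is retaken just before stimulation, so the score still measures change over one session. The risk is carry-over, not a cumulative two-session score.

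A reader might also infer that carry-over must shrink the measured effect. That is not established. The interval between sessions and the persistence of effects are not given, both arms would have had the earlier exposure, and the Introduction cites a subacute study in which subsensory stimulation did better. Carry-over could act in either direction and could differ by phase.

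Allocation is 1:1 in blocks, with separate blocks for HSR and for the two São Paulo centres, so earlier exposure should be roughly balanced between arms. A condensed article may leave terms for centre or protocol version to the analysis plan, so their absence is not held against it. A visit may also contain several sessions, although the prose gives no such mapping.

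These arguments stand and limit the claim. They do not remove the disagreement between first visit and session 3. The alternative order of sessions only moves the earlier exposure from the behavioural outcomes to the imaging outcomes.

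**Conclusion.** The concern holds in a limited form. The current text is inconsistent on the session that holds RPSS and the outcome tests, and session 3 does not fit HSR's original schedule. Two RPSS sessions at HIAE under the original schedule do not match the declared single session. As written, pre-amendment HIAE patients may have had either JTT and strength or imaging measured after an earlier session of the same stimulation.

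This is confined to HIAE patients enrolled before the amendment. HSR patients had one RPSS session under the original schedule. The article does not say whether HIAE patients still receive a second RPSS around MRI after the amendment. The number affected, the interval between sessions, and the size and direction of any carry-over are all unknown. The conclusion assumes that these patients are part of the 72, since nothing says that they are excluded. It could change once Figure 1 or the full protocol is consulted.

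**What to change.** 1. Reconcile the two parts of Interventions, the Hand Strength paragraph and Figure 1, so that for each centre and protocol version the text states which session or visit holds RPSS, the behavioural tests and the MRI. No schedule is proposed here.
2. From the visit records, derive each patient's number of RPSS exposures before each scored outcome, and report it by arm and phase.
3. Pre-specify, for the affected outcomes, a sensitivity analysis limited to patients with no earlier exposure, or a model with an exposure-by-intervention term. A main-effect covariate alone would not remove attenuation of the arm effect.
4. Where a patient had an earlier exposure, say so when describing results as those of one session.

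The cost is a text correction and one variable derived from existing records. The sample is somewhat smaller in the sensitivity analysis only; the primary analysis keeps all patients.

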### Outcome Measures

#### Primary Outcome: Change in Motor Performance After Stimulation

The primary outcome is change in the JTT performance after stimulation, compared to baseline (Figure 1): (JTT pre-stimulation – JTT post-stimulation/JTT pre stimulation) × 100. The task of copying a sentence is not performed. Previous studies showed that RPSS can enhance JTT performance and motor learning in subjects in the chronic phase after stroke (20, 29).

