### Participants

The inclusion and exclusion criteria are shown in Table 1. Subjects able to perform at least four of the tasks of the Jebsen–Taylor test (JTT) are included. The JTT scores the time (in seconds) required to perform activities often used in daily living: copying a sentence; turning over cards; picking up small common objects such as coins, bottle-cap, and paper clips; simulated feeding using a spoon; stacking checkers; and moving large light and heavy objects (32, 35).

**Table 1 T1:** Inclusion and exclusion criteria.

**Inclusion criteria**	**Exclusion criteria**
• Age ≥ 18 years • Ischemic or hemorrhagic stroke confirmed by computed tomography or magnetic resonance imaging, between 7 days and 3 months before enrollment (subacute phase), and at least 6 months (chronic phase) • Ability to perform at least 4 of 7 tasks performed in daily life that is part of the Jebsen–Taylor test; • Upper limb paresis contralateral to the lesion	• Inability to provide consent • Anesthesia of the paretic hand • Severe spasticity at the paretic elbow, fist or fingers, defined with a score larger than 3 on the Modified Ashworth Scale • Shoulder pain or join deformity in the paretic limb • Lesions affecting cerebellum, or cerebellar pathways in the brainstem • Uncontrolled psychiatric disease • Neurological diseases such as Parkinson disease or chronic uncontrolled chronic disease such as cancer or cardiac insufficiency • Aphasia or severe cognitive deficit

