#### Secondary Outcomes

Change in motor performance after training JTT is also assessed after two blocks of training (Figure 1). Changes in JTT after stimulation + training are calculated as: [(JTT post-stimulation + training – JTT pre-stimulation)/(JTT pre-stimulation)] × 100.

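### The printed primary-outcome formula is not a percent change, the post-training JTT outcome has the opposite sign, and the 4-of-7 entry rule does not match the six-task outcome

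*Protocol article*

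**What the plan says.** All references are to the protocol article.

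- **Primary outcome, in words** (Primary Outcome): "The primary outcome is change in the JTT performance after stimulation, compared to baseline".
- **Primary outcome, as a formula** (same section): "JTT pre-stimulation – JTT post-stimulation/JTT pre stimulation) × 100". One opening bracket stands before the first term. No bracket closes after the difference.
- **Post-training JTT outcome** (Secondary Outcomes): "JTT post-stimulation + training – JTT pre-stimulation)/(JTT pre-stimulation)] × 100". Here the difference is bracketed correctly, but the order is post minus pre.
- **Scale** (Participants): "The JTT scores the time (in seconds) required to perform activities often used in daily living: copying a sentence; turning over cards", followed by the remaining tasks. The score is a time, so a lower value is better.
- **Entry criterion** (Participants, Table 1): "Ability to perform at least 4 of 7 tasks performed in daily life that is part of the Jebsen–Taylor test".
- **Tasks measured** (Primary Outcome): "The task of copying a sentence is not performed". Six of the seven tasks remain.

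**The concern.** The formula is the only operational definition of the primary variable in the article, and as printed it does not match the verbal definition beside it. A programmer or reader who followed it would analyse something close to baseline JTT time multiplied by 100.

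The sign matters because the Introduction puts motor performance and motor learning together in the primary goal, with a directional hypothesis that enhancement is larger in the chronic phase. With the two JTT formulas running in opposite directions, larger enhancement means a higher value on one and a lower value on the other. The Statistical Analysis section also plans regressions of the size of behavioural improvement on baseline predictors. The sign of those coefficients depends on which formula supplies the outcome.

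The entry criterion matters because it sets how many tasks contribute to the primary variable. The article counts seven tasks at entry and six at outcome without linking the two.

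**Working it through.** **The plan's own figure.** The only related number is the sample size. 68/(1 − 0.05) = 71.6, which rounds up to 72 and agrees with the Sample Size section. The 68 cannot be re-derived because the article gives neither the SD nor the effect size as a number. No effect of the present point on power can therefore be computed.

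**The printed formula.** The JTT times below are assumed examples; the article gives none. Division precedes subtraction, so:

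- printed = (pre − post/pre) × 100
- intended = [(pre − post)/pre] × 100 = 100 − 100 × post/pre
- hence printed = intended + 100 × (pre − 1)

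Each extra second of baseline time adds 100 to the printed score, while a 10% improvement adds 10.

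| pre (s) | post (s) | printed | intended primary | secondary form, (post − pre)/pre × 100 |
|---|---|---|---|---|
| 30 | 27 | 2910 | +10 | −10 |
| 60 | 54 | 5910 | +10 | −10 |
| 120 | 108 | 11910 | +10 | −10 |
| 60 | 60 | 5900 | 0 | 0 |
| 60 | 66 | 5890 | −10 | +10 |
| 60 | 30 | 5950 | +50 | −50 |

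Three patients with the same 10% gain score 2910, 5910 and 11910. A patient who halves a 60 s time scores 5950, below the patient who goes from 120 to 108 s.

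An illustrative simulation assumed a median baseline of 60 s, log-SD 0.5, mean improvement 10% and SD 12 percentage points. The printed quantity correlated above 0.999 with baseline and about 0.01 with true percent change. The identity explains this. Under those assumptions the baseline SD is 60 × exp(0.125) × √(exp(0.25) − 1) ≈ 36 s, which contributes about 3,600 points of spread against 12 from the change itself.

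**The sign.** In the last two columns every non-zero entry is reversed. Both outcomes are on the same time scale with the same pre-stimulation denominator, so the reversal comes only from the order of subtraction.

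**The task count.** There are C(7,4) = 35 ways to be able to do exactly four of seven tasks. Of these, C(6,3) = 20 include sentence copying, and each of those leaves three of the six outcome tasks. The counts show that the case can arise. They say nothing about how often patients fall into it.

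**The case against.** The strongest reply is that the formula is a missing inner bracket and nothing more. The words say change from baseline, the factor of 100 signals a percentage, and the secondary formula is bracketed correctly, so the intent is plain. That stands, and it means the article gives no ground for saying the analysis will be run on the printed quantity. The article also carries a note of a published correction that is not shown, which may or may not touch this line. A slip in the stated definition of the primary variable still needs correcting.

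On the sign, a reader might infer bias. There is none in either test alone. The two outcomes are separate variables, and reversing one changes no p-value, effect size in absolute terms, or power. What remains is an inconsistent direction of benefit, which invites misreading and coding errors.

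On eligibility, a reader might conclude that patients with three usable tasks are being enrolled. The article does not establish this. If copying is never administered, it may not count at screening either, and the rule may already work as four of six. Even with three tasks, a within-patient percent change is defined, and nothing points to a difference between randomised arms.

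A reader might go further and infer that the set of timed tasks changes between assessments, so that a patient who regains a task shows a longer total and appears worse. The nearest text, "subjects are instructed to perform the JTT tasks that they can complete as fast as possible", describes the motor-training blocks, not how the assessments are scored. No section says that times are summed over whatever happens to be completed at each assessment. Scoring of uncompleted tasks is detail that an article may leave to the full protocol, and Data Monitoring says the study forms hold the procedures and definitions. That inference is not supported.

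**Conclusion.** The point holds in three parts of unequal weight.

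1. **The primary formula is wrong as printed.** It exceeds the intended percent change by 100 × (pre − 1), which is 5900 points at a 60 s baseline. The identity is exact; only the example times and the simulation inputs are assumed. This part must be corrected because it defines the primary variable.
2. **The two JTT outcomes have opposite signs for the same improvement**, +10% against −10% for 60 to 54 s. This affects interpretation and the planned regressions on improvement, not the validity of either comparison.
3. **The entry rule and the outcome count different task sets.** Read literally, three of six outcome tasks is possible. Whether that reading is the one applied cannot be told from the article.

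The point does not show that any analysis has been or will be done wrongly, that either arm is favoured, or that 72 patients is the wrong number.

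**What to change.** - Define both JTT outcomes as [(pre − post)/pre] × 100, where post is the post-stimulation time for the primary outcome and the time after stimulation plus training for the secondary. State once that positive values mean improvement.
- Use that convention in the group comparisons and in the regressions of improvement on baseline predictors.
- Reconcile Table 1 with the Primary Outcome section by stating whether sentence copying counts toward the four tasks required for entry. Because recruitment began in December 2019, the statement should describe the rule actually applied and should not be used to remove patients already randomised.

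The cost is two formula lines and one sentence. The formulas can be applied to JTT times already recorded, and neither the sample size nor the randomisation changes.
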